## Abstract

**Background:**

Socio-economic inequities can strongly influence suboptimal infant feeding outcomes. Factors such as lack of knowledge about breastfeeding, low family income, low educational attainment, social and economic status, cultural norms and ethnicity may negatively affect success with offering breastfeeding following a responsive feeding approach (ie. responsive breastfeeding). Such inequities can indeed shorten breastfeeding duration, and negatively affect behavioral and cognitive infant outcomes. In China, there is a dearth of studies focusing on breastfeeding from the responsive and health equity perspective.

**Objective:**

The aim of this article is to present a protocol of an ongoing longitudinal cohort study investigating factors associated with responsive breastfeeding behaviors, and the child’s behavioral and cognitive development from birth to12 months post-partum in five centers in China. The study seeks to identify breastfeeding barriers and facilitators from a health equity perspective.

**Methods:**

We are enrolling 700 women and their singleton full term infants in Chongqing, Huizhou and Guangzhou urban and rural areas. The study questionnaires will be administrated within 72 h, 30 days, 3, 6, 9, and 12 months post-partum during the baby’s vaccination visits. We will investigate the difference between urban and rural areas sociodemographic characteristics, breastfeeding knowledge, attitudes and practice, postnatal depression, maternal emotion regulation and parenting stress, and anthropometric and cognitive development indicators of the infants at each time-point.

**Conclusion:**

Our article illustrates how a cohort study can be designed to understand the barriers and facilitators of responsive breastfeeding taking equity principles into account to help promote infants’ growth and development in China.

## Background

In the past ten years, health equity has been emphasized more in the maternal-child care research agenda. Health equity underlies a commitment to reduce—and, ultimately, eliminate—disparities in health and in its determinants, especially the social determinants [1]. Pursuing health equity means striving for the highest possible standard of health for all people and giving special attention to the needs of those at greatest risk of poor health, based on social conditions [2]. This approach is crucial for human development as child malnutrition and poor health are intimately linked with each other and with suboptimal child growth and development [3].

Breastfeeding is beneficial to the health of mothers as well as their infants, including their overall development [4]. Indeed, breastfeeding can prevent infections and malocclusions, improve infants’ intelligence, and may reduce the risk of overweight and diabetes among children [5]. In addition, protecting, promoting and supporting breastfeeding is critical to achieving the sustainable development goals (SDG) in low- and middle-income countries by 2030 [6], including the tenth goal of SDG, which is to reduce inequality [5]. Previous studies have evaluated the barriers to breastfeeding [7] and the effectiveness of strategies to promote it [8, 9]. However, there is a dearth of studies designed on how to support breastfeeding and other aspects of responsive feeding from the health equity perspective in China.

Protecting, promoting and supporting breastfeeding requires overcoming major health care and social protection systems challenges worldwide. In China, a wide range of social determinants of health, as well as psychological and geographical factors have been identified as barriers for exclusive breastfeeding [7, 10–12]. A cross-sectional study conducted in China identified as key factors for breastfeeding: breastfeeding education, family support, health care institutional policies and practices that are conducive to breastfeeding, paid maternity leave and other maternity protection benefits [13]. Indeed, a quasi-experiment study in China found that increasing breastfeeding rate requires family-centered breastfeeding education and support [10]. Another study reported that most mothers encountered breastfeeding barriers that might interrupt exclusive breastfeeding when they left the health facility [14] and that pre- and post-natal breastfeeding education and supporting form healthcare providers are needed to facilitate and sustain breastfeeding.

Mother’s psycho-emotional status also affects breastfeeding outcomes. Postpartum stress has been shown to affect infant growth, nutrition, bonding, temperament and ultimately mental wellbeing during childhood [15]. The association between mother’s psychological health and infants’ cognitive behavior is noteworthy. For example, higher maternal paranoid ideation may delay language and cognitive development. Furthermore, maternal hostility and anxiety increase gross motor developmental delays, and maternal depression leads to overall development delays in infants [16].

Responsive feeding (RF), defined as “feeding practices that encourage the child to eat autonomously and in response to physiological and developmental needs, which may encourage self-regulation in eating and support cognitive, emotional, and social development” [17], is an aspect of responsive parenting that contributes to a nurturing and caring environment for children [18]. RF principles can guide parents on how to feed their young children, which complements existing global guidance on what to feed them [17, 18]. Parents who practice RF identify and respond to their infants’ hunger and satiety cues in a nurturing manner, fostering healthy eating habits and self-regulation, and reducing excessive weight gain risk [19]. The nurturing environment created by RF has immense potential for improving child growth and development outcomes [20], especially in settings such as China where poverty and malnutrition in all its forms (including stunting, overweight/obesity, and micronutrient deficiencies) coexist [21].

The 2016 Lancet Early Childhood Development Series highlighted that a lack of nurturing care in early childhood, including responsive parenting and feeding, can have lifetime health, developmental, and productivity implications [22]. There is a paucity of evidence on how best to design and deliver home-based parenting skills interventions that have been shown to be key for improved child psycho-emotional, social and cognitive development [23], with its benefits extending to adulthood [24].

Breastfeeding research in the context of RF has become a priority given the vital role that breastfeeding plays in infants’ growth and development, including cognition [25]. Even though the relationship between breastfeeding and improved cognition has been documented for decades across different countries [25–27], few countries have operationalized breastfeeding promotion programs in the context of nurturing care. Research is needed to understand how best to do so as globally breastfeeding services remain fragmented and of relatively low quality. Furthermore, programs at scale are rare and poorly evaluated.

### Aims and objectives

At present, there is still a dearth of research to explore simultaneously factors influencing breastfeeding and early childhood development. This work is needed to understand how best to integrate maternal-child health, nutrition and development programs. We are unaware of studies that have been conducted in China to address this knowledge gap. In order to fill this research gap, we designed a multi-center longitudinal cohort study from birth to 12 months of age taking health equity principles into consideration with the goals to: a) to understand RF barriers and facilitators including those related to breastfeeding, and b) determine the association between breastfeeding and infant development in China. The study’s research hypotheses are that in Chinese households: 1) there are barriers to responsive feeding, driven by the social determinants of health, 2) suboptimal responsive feeding can shorten the duration of breastfeeding and delay infant’s growth and development.

## Methods/ design

### Study design: multi-center prospective longitudinal study

We will follow up women who delivered a singleton full term infant of age at 72 h, 30 days, 3 months, 6 months, 9 months and 12 months after birth, with these time points corresponding to each of the six study waves. At each point we will collect information on maternal knowledge, attitude and practice (KAP) towards breastfeeding, postnatal depression, emotional regulation and parenting stress. We will use questionnaires responded by the mothers to assess their psychological status and emotional regulations, and we will extract data from the infants’ medical charts to assess their growth and cognitive development. The recruitment of participants began in July 2019 and is currently on hold due to the coronavirus disease 2019 (COVID-19) pandemic. This study was registered at the Chinese Clinical Trial Registry (ChiCTR) (record ID; http://www.chictr.org.cn (ChiCTR2100044028)).

### Study setting

We have started recruiting participants from five public health institutions in Chongqing municipality, Guangzhou city and Huizhou city of Guangdong province representing Southern China. Public hospitals in China have more economic resources and advanced technology than private facilities, hence the public health care system is able to provide more comprehensive and effective medical services than the private health care system. Center one, Chongqing Health Center for Women and Children is located in Yubei district, Chongqing, western China, it serves over 10,000 infants in the regions annually. Center two, Tianhe District Maternal and Child Hospital of Guangzhou is located in Tianhe district, Guangzhou, that serves 1500–2000 deliveries annually. Centers three to five are primary health facilities that jointly represent Huizhou city in our study, namely Huidong County Maternal and Child Health Service Center, Tieyong Town Health Center and Duozhu Town Health Center. Centers one and two targets urban population and the third center serves a mixed urban and rural population. Centers four and five targeting rural populations, located in Huidong county. The diversity of populations represented on our study sample that includes western and eastern of China and both rural and urban areas will facilitate our aim to understand breastfeeding risk factors from the health equity perspective (Fig. 1).

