### Sample size calculation

From the perspective of health equity, we designed the study to enroll participants from rural and urban areas. We estimate the sudy sample size based on the different prevalences of breastfeeding in urban an rural areas.

The sample size was calculated using the following formula for comparison of two proportions:
$$ {\mathrm{n}}_{\mathrm{urban}}={\mathrm{n}}_{\mathrm{rural}}=\frac{{\left[{\mathrm{Z}}_{1-\upalpha /2}\sqrt{2\overline{\mathrm{p}}\left(1-\overline{\mathrm{p}}\right)}+{\mathrm{Z}}_{\upbeta}\sqrt{{\mathrm{p}}_1\left(1-{\mathrm{p}}_1\right)+{\mathrm{p}}_2\left(1-{\mathrm{p}}_2\right)}\right]}^2}{{\left({\mathrm{p}}_1-{\mathrm{p}}_2\right)}^2} $$where *n*_urban_ and *n*_rural_ are the sample sizes corresponding to the urban and rural groups, respectively; *Z*_*1-α/2*_ and *Z*_*β*_ are the Z values corresponding to the alpha (*α*) and beta (*β*) error, respectively; *p*_1_ and *p*_2_ are the estimated proportion of breastfeeding rates in urban and rural areas, respectively, while $$ \overline{p} $$ is the average of *p*_1_ and *p*_2_.

According to the China Development Research Foundation (CDRF) 2019 *Report on National Survey of Factors Influencing Breastfeeding*, the prevalence of breastfeeding during the first six months of life in large cities (estimated *p*_1_) and medium/small cities (estimated *p*_2_) was 36 and 23%, respectively. With a statistical power of 90% and a two-tailed significance level of 5%, we estimated that a minimum of 257 participants for each group (urban and rural), should be recruited respectively. Therefore, a sample of 514 are required to observe a 13% difference in the prevalence of breastfeeding between the two groups. Taking into consideration that 25% participants may be lost to follow-up, our goal is to enroll 700 participants.

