### Measurement of outcomes, independent variables and covariates

The outcome indicators are based on growth and developmental indicators such as infants’ weight, length, and child development score based on the Caregiver Reported Early Childhood Development Instruments (CREDI) [35].

The key independent variables are the following mother’s RF-related behaviors: mother’s KAP towards breastfeeding including exclusive breastfeeding or not; duration of breastfeeding; pressuring child to eat, restricting what child eats, and responsive styles according to infant feeding style questionnaire (IFSQ) [31]; postnatal depression scores; emotion regulation scores; parenting stress scores.

The co-variates included are based on household socio-demographic data including socioeconomic status and household geographical location and corresponding health center.

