### Statistical analysis

Descriptive analysis will be performed to describe the socio-demographic characteristic of the participants and to summarize the scale scores of the questionnaires. In order to identify the inequity factors of RF, the crude and adjusted breastfeeding rates for urban or rural residence and the associations between RF and early childhood development outcomes will be estimated with their corresponding 95% confidence intervals (95% CI). Continuous variables will be presented as mean with standard deviation (SD) or median with interquartile range (IQR). After testing for the normality of the distribution means will be compared using Student’s t test or analysis of variance. Categorical variables will be presented as counts with percentages and compared using Person’s χ^2^ test or Wilcoxon rank-sum test between groups, such as urban and rural.

For the cross-sectional analysis of the data, logistic regression and linear regression will be performed to identify barriers and facilitators of RF or infant growth and development, respectively. Interactions among the latent influencing factors will be performed using multivariable analysis to test for potential effect modification taking inequities indicators into account, such as socioeconomic status, psycho-emotional status and maternal health care access. For the longitudinal data analysis, linear mixed effect model or multilevel mixed-effects models will be performed to determine the association between RF and infant growth and development after adjusting for time dependent and static covariates. The statistical significance will be considered as a two-tailed *p* value ≤0.05. All data will be analyzed using Statistical Analysis System (SAS Institute Inc., Cary, North Carolina, USA).

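### Urban/rural status is nearly confounded with center, yet the sample-size formula and the urban-rural tests treat mothers as independent

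*Protocol article*

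**What the plan says.** Under Study setting, the protocol article describes five centers: "Centers one and two targets urban population and the third center serves a mixed urban and rural population". It continues: "Centers four and five targeting rural populations, located in Huidong county". Centers three to five are primary health facilities that together represent Huizhou; the two urban centers are in Chongqing and Guangzhou.

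Under Sample size calculation, the study is sized on the urban-rural difference in breastfeeding prevalence: "The sample size was calculated using the following formula for comparison of two proportions". The design values are "With a statistical power of 90% and a two-tailed significance level of 5" percent, with prevalence that "was 36 and 23%, respectively" in the two groups. The result is stated as "we estimated that a minimum of 257 participants for each group (urban and rural"), 514 in all, raised to 700 for 25% loss. No term for center appears.

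Under Statistical analysis, means are compared by t test or analysis of variance, and categorical variables by a chi-square "test or Wilcoxon rank-sum test between groups, such as urban and rural". Crude and adjusted breastfeeding rates by residence are promised, with no adjustment set named. Mixed or multilevel models are named only for responsive feeding against infant growth and development.

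The covariates, listed under Measurement of outcomes, independent variables and covariates, include "household geographical location and corresponding health center". The outcomes named in that section are infant weight, length and the development score.

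**The concern.** In four of the five centers, knowing the center tells you whether a mother is urban or rural. Any difference between centers in staffing, feeding policy, facility level or region then goes straight into the urban-rural difference. A formula or test that counts each mother as an independent observation leaves this source of variation out. Its standard error is too small, so the true power is lower and the true type I error higher than stated.

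Zero between-center variation is hard to assume here. The Discussion itself expects regional differences in health-care access, quality and culture to affect breastfeeding, and reports that recruitment and follow-up already differ by center. What is at stake is that an ordinary center difference gets reported as an urban-rural inequity.

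**Working it through.** **Inputs from the article.** p1 = 0.36, p2 = 0.23, two-sided alpha 0.05, power 0.90, 257 per group, 514 in total; two urban centers, two rural, one mixed.

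**Assumptions, not in the article.** Five equal centers of 514/5 = 102.8 analysed mothers; center three split evenly by residence; center ICC ρ between 0.005 and 0.05.

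**1. The article's own figure.** With mean proportion 0.295:

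n = [1.960 × √(2 × 0.295 × 0.705) + 1.282 × √(0.36 × 0.64 + 0.23 × 0.77)]² / 0.13² = (1.264 + 0.818)² / 0.0169 = 256.5, so 257.

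Power at 257 per group is 90.05%. The total 514/0.75 rounds up to 686, and 700 covers it. The stated figures are reproduced, at ρ = 0.

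**2. Design effect for this layout.** The urban mean gives centers one, two and three weights 0.4, 0.4 and 0.2. The rural mean gives centers three, four and five weights 0.2, 0.4 and 0.4. Center three cancels in the difference, leaving four weights of ±0.4, whose squares sum to 0.64. Hence

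Var(difference) = σ² × [0.64ρ + (1 − ρ) × 2/257],

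and, relative to the independent-mothers variance 2σ²/257,

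DE = (1 − ρ) + 0.64 × (257/2) × ρ = 1 + 81.24ρ.

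Power comes from the two-proportion formula at 257/DE. The naive test's type I error is 2 × [1 − Φ(1.96/√DE)].

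| ICC | DE | Effective n per group | Power | Naive type I error |
|---|---|---|---|---|
| 0 | 1.00 | 257 | 90% | 5% |
| 0.005 | 1.41 | 183 | 78% | 10% |
| 0.01 | 1.81 | 142 | 67% | 15% |
| 0.02 | 2.62 | 98 | 51% | 23% |
| 0.05 | 5.06 | 51 | 30% | 38% |

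Beta-binomial simulation of the same layout gives type I errors that agree with the last column to within about one percentage point.

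For scale, ρ = 0.01 is a between-center standard deviation of √(0.01 × 0.295 × 0.705) = 4.6 percentage points.

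**3. Can more mothers at the same centers restore 90%?** Setting N/DE(N) = 257, with DE(N) = (1 − ρ) + 0.32Nρ, gives N = 257(1 − ρ)/(1 − 82.24ρ) per group.
- ρ = 0.005: 255.7/0.589, about 435 per group.
- ρ = 0.01: 254.4/0.178, about 1,433 per group.
- ρ above 1/82.24 = 0.012: no sample size suffices.

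**4. The conditional case: center as a fixed effect in the urban-rural model.** Residence does not vary within centers one, two, four and five, so only center three contributes.
- With equal centers and an even split, about 20% of the information on residence remains; with a 25:75 split, about 15%.
- Power for 36% versus 23% is about 30% at 51 versus 51 mothers, and 22% if center three yields only 35 versus 35.

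**The case against.** - **The loss rests on an ICC that the article does not give.** This stands. If the ICC were zero, the stated power and error rate would hold. At 0.005 the loss is moderate, at 78% power. But the article gives no ground for assuming zero, and its Discussion points the other way.
- **A reader might infer that adjusting for center removes the contrast altogether.** The documents do not support that. Center three is mixed, so a within-center comparison survives, weak but not nil.
- **A reader might also take the covariate list as the plan for the adjusted urban-rural rates.** The text does not say so. The list stands beside growth and development outcomes, no adjustment set is named for the breastfeeding rates, and nothing says center enters as a fixed effect. An unseen full protocol or analysis plan may settle this. It is an open risk, not a stated error.
- **Urban-rural is not a stated hypothesis.** True: the two hypotheses under Aims and objectives concern barriers to responsive feeding and its consequences. The contrast is, however, the only basis for the sample size and a named comparison.
- **The textbook design effect, 1 + (102.8 − 1)ρ, would show a larger loss** (power 62%, 46% and 26% at ICC 0.01, 0.02 and 0.05). It ignores that an evenly split center three cancels, so the smaller losses in the table are the right ones for this layout.
- **Multilevel models are already named.** Only for responsive feeding against growth and development, and without saying that center is a level. They do not cover the urban-rural breastfeeding comparison.

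**Conclusion.** The concern holds in this form: urban/rural status is nearly confounded with center, and the power calculation and the named urban-rural tests make no allowance for it. The 257 per group is right on its own inputs, but its 90% power and the nominal 5% error apply only at a center ICC of zero. Over an assumed ICC of 0.005 to 0.05, with equal centers and center three split evenly, power runs from about 78% down to 30% and the type I error of the naive test from about 10% up to 38%. Uneven centers or a different split would change these values.

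The fixed-effect problem is secondary and conditional. It arises only if center is entered that way in the urban-rural model, and would then leave power of roughly 22% to 30%. Because the article itself fixes the center layout, the formula and the tests, a later analysis plan could change the analysis but could not make the stated power correct.

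**What to change.** 1. Under Sample size calculation, restate the power for the urban-rural contrast over a stated ICC range, with the assumed number and size of centers and the split in center three.
2. Under Statistical analysis, for the urban-rural breastfeeding contrast, define residence at household level and fit center as a random intercept with small-sample degrees of freedom, not as a fixed covariate. Keep the chi-square, rank-sum and t tests as description only.
3. Report the urban-rural comparison within center three as a sensitivity analysis.
4. Word the conclusion as a difference between the catchments of these five centers. The Discussion already concedes that they do not represent all regional variation.

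**Cost.** No new data are needed, and with 104 of 700 mothers enrolled and recruitment suspended at the time of writing, the change can still be made. Intervals will be wider, and five centers estimate the between-center variance poorly. As a rough guide, a t reference with 5 − 2 = 3 degrees of freedom gives about 60% power at 257 per group even with an ICC of zero. The restated power will be lower than 90%. More mothers at the same centers cannot practically restore it at an ICC of about 0.01, and cannot restore it at all above about 0.012 under the layout assumed here.
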